## Methods

### Study Design

Following screening, informed consent, and baseline assessment, participants (N=195) are randomized (1:1:1) into: PHN alone (n=65), SMS text messaging alone (n=65), or combined PHN+SMS text messaging (n=65). The 3-arm repeated-measures design will assess participants at baseline, 3 (immediate effects), 6, 12 (sustained effects), and 18 (distal effects) months post randomization to determine the relative effectiveness of the interventions, including heterogeneous treatment effects across subgroups and over time, the implementation and sustainment costs of each intervention, and their cost-effectiveness relative to one another. The study uses an “intent-to-treat” design whereby all assessments are administered to all participants regardless of their level of participation or retention in the study (Figure 1).

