The primary outcome of the cost-effectiveness analysis (Aim 3) will be the incremental cost-effectiveness ratio (ICER), which will be calculated as the incremental, predicted-mean cost of a given intervention relative to an alternative, divided by the incremental predicted-mean effectiveness of the 2 interventions. The primary measure of effectiveness for the economic evaluation will be QALYs. The secondary measure of effectiveness will be advancement along the HIV Care Continuum. The QALY is a measure that combines the health-related quality-of-life associated with an individual’s health state and the time spent in that state and is recommended as the primary effectiveness measure in economic evaluation studies due to its ability to be compared across interventions and disorders [58,63]. In addition, generally accepted thresholds for defining value have been established for QALYs, unlike clinical measures [64,65]. The HIV Care Continuum is an important and widely accepted model or tool for assessing HIV care outcomes at both an individual and a public health level; thus, the additional cost required to achieve a one-step increase along the HIV Care Continuum for the average transgender woman with HIV will be a critically important clinical and policy-relevant measure. Two ICERs (one for each effectiveness measure) will be calculated for each stakeholder perspective at both 3 months (intervention completion; immediate effects) and 18 months (distal effects).

To help address censored data, we will model the person period and estimate all regressions using a multivariable GLMM. Separate regressions will be estimated to predict the mean value for each resource category, at each time period, by study arm. The statistical method of recycled predictions will be used to obtain the final predicted mean values [58]. Similarly, individual regressions will be used to predict the health utility index value and HIV Care Continuum steps gained for each participant, at each time point. QALYs gained will be estimated using the predicted health utility values and the area under the curve methodology [58]. The most appropriate distributional and link functions for each GLMM regression will be chosen according to the fit of the observed data [58].

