To account for sampling uncertainty in point estimates, the *P* values and SEs will be estimated using nonparametric bootstrapping techniques within the multivariable framework combined with methods to address missing data based on recommended approaches [66]. All monetary values will be adjusted for inflation, and all measurements obtained beyond 12 months of baseline will be discounted for time preference using the recommended rate of 3% [58,65].

The most cost-effective strategy for each outcome measure (QALYs; HIV Care Continuum placement) will be determined using the rules of strong and extended dominance. Parametric methods based on parameters obtained from bootstrapping will be used to estimate cost-effectiveness acceptability curves for each ICER, which illustrate the probability that an intervention is cost-effective for different value thresholds [57].

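### The acceptability curves are tied to two-arm ICERs, so they do not express the uncertainty of a choice among three arms

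*Protocol article*

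**What the plan says.** All statements are in the protocol article.

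- **Competing strategies.** Study Design has three parallel arms of 65: PHN alone, SMS alone and the combination.
- **ICER.** Statistical Analyses, Aims 2 and 3, defines it as "the incremental, predicted-mean cost of a given intervention relative to an alternative, divided by the incremental predicted-mean effectiveness of the 2 interventions". This is a two-arm quantity.
- **Count of ICERs.** "Two ICERs (one for each effectiveness measure) will be calculated for each stakeholder perspective at both 3 months" and again at 18 months. The pair of arms entering each ratio is not named.
- **Selection rule.** "The most cost-effective strategy for each outcome measure (QALYs; HIV Care Continuum placement) will be determined using the rules of strong and extended dominance". This ranks all three arms.
- **Uncertainty.** The next sentence names a parametric approach that draws on the bootstrap, "used to estimate cost-effectiveness acceptability curves for each ICER, which illustrate the probability that an intervention is cost-effective for different value thresholds".

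The article describes no probability that an arm is the best of the three.

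**The concern.** The decision has three options, but the one measure of decision uncertainty that the article describes is attached to a ratio of two. A two-arm curve answers whether A is worth choosing over B. It does not answer whether A should be chosen when C is also available. Separate two-arm curves need not give probabilities that sum to one over the arms, and two arms can both look probably cost-effective, each against a weaker comparator.

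The article names providers, insurers and policy makers as the audience. If they are handed these curves alongside the selected strategy, they have no figure for how likely that selection is to be right. The figure they do have can only err on the high side for that purpose.

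**Working it through.** The article states no number for the curves, so there is nothing to reproduce. The check has a general part and an illustration.

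**1. Direction, for any data.** Write NMB = λ × effect − cost for each arm at threshold λ. The event that A beats both B and C is contained in the event that A beats B, and in the event that A beats C. Hence

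P(A best of three) ≤ min[P(A > B), P(A > C)].

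A two-arm curve therefore never lies below the best-of-three probability.

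**2. Size, under an assumed model.** Assume that the mean NMBs of the arms are independent and normal with a common standard error s. Then

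- P(A > B) = Φ[(μA − μB) / (s√2)]
- P(A best) = ∫ φ(z) Φ(z + (μA − μB)/s) Φ(z + (μA − μC)/s) dz

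Mean NMBs below are in units of s√2, the standard error of a two-arm difference.

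| Mean NMB of three arms | Top arm vs lowest | Top arm vs next | Top arm best of three |
|---|---|---|---|
| 0, 0, 0 | 0.50 | 0.50 | 0.33 |
| 0, 0, 0.5 | 0.69 | 0.69 | 0.55 |
| 0, 0.5, 1 | 0.84 | 0.69 | 0.63 |
| 0, 1, 1 | 0.84 | 0.50 | 0.47 |
| −3, 0, 0.5 | 1.00 | 0.69 | 0.69 |

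An arm at 0.75 against each of two equal rivals is best with probability 0.62. At 0.80 it is best with 0.69.

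Two features matter. Against the closest rival, the gap runs from about zero (last row, third arm out of contention) to 0.50 − 0.33 = 0.17 (equal arms). Against a weak comparator it can be larger: in the fourth row, both upper arms show 0.84 against the lowest arm, yet each is best with only 0.47.

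**3. The same on a cost and QALY scale.** Every input here is assumed except n = 65 per arm: mean costs 500, 2,500 and 3,000 and QALYs 0.80, 0.84 and 0.86 for SMS, PHN and the combination; SDs 8,000 and 0.25; cost and effect uncorrelated.

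At λ = 100,000:

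- NMB: SMS 80,000 − 500 = 79,500; PHN 84,000 − 2,500 = 81,500; combined 86,000 − 3,000 = 83,000
- s = √[(100,000 × 0.25)²/65 + 8,000²/65] ≈ 3,256, so s√2 ≈ 4,604
- PHN vs SMS: Φ(2,000/4,604) = 0.67
- Combined vs SMS: Φ(3,500/4,604) = 0.78
- Combined vs PHN: Φ(1,500/4,604) = 0.63
- Best of three: SMS 0.13, PHN 0.32, combined 0.55

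PHN shows 0.67 on its curve against SMS, although it is the best arm with probability only 0.32. At λ = 50,000 the combination shows 0.58 against each rival and 0.41 for best of three.

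**The case against.** - **The two-arm unit is inferred.** The article never says that curves are drawn per pair of arms. It counts ICERs by effectiveness measure, perspective and time: 2 × 3 × 2 = 12. Three pairs per cell would give 36, and two frontier steps per cell 24. One could therefore read the curve sentence as a set of curves per cell, perhaps one per arm. This stands as a limit on certainty. Even so, the article's own definition makes an ICER a ratio of two interventions, and the curves are attached to that object, so the two-arm reading is the natural one.
- **The article does not claim a best-of-three probability.** A reader might infer that it presents the curves as the probability of being the most cost-effective arm, and so misstates certainty outright. The text does not support that: it says only cost-effective, and a two-arm curve answers a two-arm question correctly. The problem arises when the curves serve the three-way choice announced in the sentence before.
- **Dominance already handles three arms.** It does, as a ranking. A reader might infer that it is applied to point estimates with no uncertainty. The article does not say so, nor does it say that the ranking is repeated over bootstrap replicates. Curves for the ICERs left after dominance would still compare two arms at a time.
- **An unseen health-economic plan may define joint curves.** It may. But the article does more than leave detail out: it states the unit of the curve, and that unit does not fit the stated decision.
- **The size is not from this trial.** Correct. The gap may be negligible if one arm proves clearly inferior.

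**Conclusion.** The concern holds as a mismatch between a two-arm measure of uncertainty and a three-arm decision. It rests on reading the curves through the article's own ICER definition, which is the natural reading but not the only possible one. The direction is certain for any data: the two-arm probability is at or above the best-of-three probability. The size cannot be computed from the article. Under the assumed model, the excess over the closest two-arm comparison ranges from near zero to 0.50 against 0.33, and a curve against a weak comparator can be further off. The article describes the comparative effectiveness of the interventions as not yet evaluated, so it gives no ground for expecting the near-zero end. Only the reported uncertainty for Aim 3 is affected, not the viral suppression analysis. The change should be made, but the trial does not depend on it.

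**What to change.** Define the acceptability curves over all three arms. From the planned bootstrap, or from the parametric joint distribution of arm-level costs and effects that it yields, compute the net monetary benefit of PHN, SMS and the combination together. At each threshold report each arm's probability of having the highest value (three curves summing to one), with the acceptability frontier. Do this for each effectiveness measure, perspective and time point. Keep ICERs, computed sequentially after strong and extended dominance, as descriptive output, and name the pair of arms in each.

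The parametric route can stay, provided that the draws are joint across arms. The cost is slightly more analysis work, and the reported probabilities may look less favourable. No data, visits or participants are added. Data collection is expected to run to July 2027, so the change can be fixed before analysis begins.

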#### Power Analysis

A simulation approach was used to conduct the power analysis and determine that N=195 (65 per arm) was an appropriate sample size to detect the effect of each intervention on our primary outcome, and the likelihood of virologic suppression over time [67]. Power by simulation is more flexible than traditional approaches because it can estimate power under a wide variety of circumstances, including when these assumptions are not met.

### Ethical Considerations

All study procedures are approved by the Western Institutional Review Board (Study #1352118; Institutional Review Board Tracking #20231531). This trial has been registered at ClinicalTrials.gov under the number NCT06408350. All procedures performed in studies involving human participants were in accordance with the ethical standards of the institutional or national research committee and with the 1964 Helsinki Declaration and its later amendments or comparable ethical standards. Informed consent was obtained from all individual participants included in the study.

## Results

Recruitment began on April 10, 2024, and the first participant was enrolled on April 11, 2024. Recruitment spans approximately 33 months; enrollment goals are approximately 6 enrolled participants per month. Data collection, including all follow-up assessments, is expected to be completed in July 2027.

## Discussion

### Principal Findings

Many transgender women have suboptimal advancement through the HIV Care Continuum, including poor HIV health care usage, retention in HIV medical care, and rates of viral suppression; moreover, these issues are exacerbated by comorbid conditions such as SUDs. The Text Me, Alexis! study is a comparative-effectiveness research trial with a comprehensive economic evaluation that builds upon the promising findings of two Health Resources and Services Administration-funded demonstration projects in order to identify the optimal intervention for advancing transgender women with HIV to full viral suppression. Though the effectiveness of the demonstration projects has been established, their comparative effectiveness, required resources or costs, cost-effectiveness, and heterogeneous effects on subgroups, including those with SUDs, have not been evaluated.

### Challenges

There are several challenges to the Text Me, Alexis! study. First, housing instability, substance use, engagement in sex work, and other individual-level, social, and structural disparities may interfere with study participation. The PHN alone and PHN+SMS text messaging arms were designed to address these issues and work with each participant to assess and minimize or remove barriers and link participants to an array of ancillary social services. Additionally, in the demonstration project, despite experiencing several health disparities including low educational attainment, low income, and housing instability, SMS text messaging alone demonstrated significant improvements in ART uptake, ART adherence, and achievement of an undetectable viral load, which were durable through 18-month follow-up. Second, episodes of short-term incarceration may interrupt study progress and follow-up assessment rates, due to factors such as actual or perceived participation in the street economy, or minor homeless infractions. Study staff monitor the public records database for participants who miss appointments. When an incarcerated participant is found, we begin a correspondence with the participant immediately upon release. Third, loss of ART or selling ART due to lifestyle needs (“diversion”)—ART adherence will be stressed through the participant-centered treatment plan and via adherence-specific SMS text messages, including strategies for keeping medication safe, and a discussion on how ART adherence outweighs selling the drug. Finally, fear of drug-drug interaction—some participants may be concerned about ART and gender-affirming hormone therapy interactions and prioritize gender-affirming hormone therapy over ART uptake or adherence. These concerns will be acknowledged and corrected in PHN sessions and SMS text messages.

### Conclusions

The public health significance of Text Me, Alexis! has the potential to be quite profound, as comparative- and cost-effectiveness research trials are critical steps in the development and adoption of scalable and effective HIV care intervention, especially among key populations that rely on service provision in resource-limited, community-based settings.

## Appendix

Multimedia Appendix 1 Summary Statement Peer Review Comments.

## Abbreviations

ART: antiretroviral therapy
DSM-5: Diagnostic and Statistical Manual of Mental Disorders (Fifth Edition)
GLMM: generalized linear mixed model
HBM: health belief model
HIV-ASES: HIV Treatment Adherence Self-Efficacy Scale
ICER: incremental cost-effectiveness ratio
ISSB: Inventory of Socially Supportive Behaviors
LAC: Los Angeles County
PHN: peer health navigation
PROMIS: Patient-Related Outcome Measurement Information System
PROPr: PROMIS-preference score
QALY: quality-adjusted life-year
SCT: social cognitive theory
SST: social support theory
SUD: substance use disorder
